To address these knowledge gaps our team conducted the Congenital Heart Adolescents Participating in Transition Evaluation Research (CHAPTER 1) Study [16] to evaluate a single-session nurse-led transition education intervention, focusing on CHD knowledge, for youth 15–17 years of age. This study significantly improved patients’ knowledge of their CHD lesion in the intervention group at one month, which was sustained at 6 months. The intervention group also had higher self-management skills at six months, even though self-management skills were not the focus of the intervention. Limitations of this study include enrollment at a single center and use of surrogate outcomes (questionnaires) rather than participant behaviors such as attendance at an ACHD clinic. The current study was designed to build upon our experience with CHAPTER 1, specifically to include a self-management component of the intervention, to document time to first ACHD clinic appointment, and to assess generalizability of the intervention across more than one clinical program.

The primary aim of the CHAPTER 2 study is to determine the impact of a nurse-led intervention on time to first ACHD clinic attendance among youth graduating from one of two quaternary-care pediatric cardiology programs. We hypothesize that the transition intervention in combination with usual care will result in superior timing of the first ACHD clinic attendance compared to usual care alone. Secondary aims are to describe: 1) change in adolescent knowledge of their CHD, 2) change in self-management and self-advocacy skills using validated instruments [17, 18], 3) Incidence of cardiac procedures post enrollment, and 4) the frequency and content of verbal and written (email/text messaging) dialogue between nurse and participant.

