### Secondary outcomes

Given the complex, multidimensional nature of the transition process, transition interventions need to consider multiple outcomes, including cognitive factors (e.g. CHD knowledge) and self-management behaviours. Therefore, several secondary outcomes are proposed. All baseline questionnaires will be completed in the pediatric clinic, and prior to Session One for those in the intervention arm.Change in MyHeart scores between baseline, 1, 6, 12 and 18 months. The MyHeart scale consists of eight questions that assess participant’s knowledge of their cardiac condition. The MyHeart scale was developed for the CHAPTER 1 study, with a significant improvement in score observed at 1 and 6 months post intervention, compared to participants in the usual care group [16].Change in Transition Readiness Assessment Questionnaire (TRAQ) score between baseline, 1, 6, 12, and 18 months. The TRAQ is the most rigorous transition readiness scale for adolescents. Sawicki et al. identified behaviours relevant to transition, tested item reliability and validity, and then field tested the items with 194 youth with special healthcare needs [18]. Scores range from 0 to 5. Principal component factor analysis revealed two domains explaining 68 % of the total variance: self-management (16 items, mean score 3.01 ± 1.02) assessing skills such as filling prescriptions, understanding treatment side effects, and arranging medical follow-up visits; and self-advocacy (13 items, mean score 3.67 ± 0.77) assessing communication skills with the healthcare team, managing activities of daily living, and use of school and community resources. Internal consistency is high, with Cronbach’s alpha of 0.92 (Self-management) and 0.82 (Self-advocacy). A ceiling effect is unlikely given the mean scores noted above. The reading level is Grade 5.7 and this instrument takes ~5 min to complete. The 12 and 18 month assessments will provide longitudinal data on evolution of self-management and self-advocacy skills and will allow participants in the intervention group sufficient time to apply the skills gained (e.g., to independently book a physician appointment).Change in the Williams’ Scale between baseline, 1, 6, 12, and 18 months. The Williams’ scale is a measure of medical self-management and transition readiness among adolescents with special health care needs, having high internal consistency (Cronbach’s alpha 0.89) [17]. This consists of 21 Likert-scaled items and has a grade 4.9 reading level.Assessment of patient engagement via a cardiologist questionnaire. This questionnaire will be completed by the participant’s primary cardiologist at the first cardiology clinic visit (pediatric or adult site), after month 3 post enrollment. This questionnaire will help determine if those participants in the intervention group were more engaged with their cardiologist then those in the usual care group. The single-page questionnaire consists of six items and takes 1–2 min to complete.Incidence of cardiac re-intervention (surgery or interventional catheterization). Chart review at 12 and 24 months post enrollment will be done independently by two RNs who will be blinded to group allocation. This review will ascertain cardiac hospitalizations and invasive cardiac procedures (since study enrollment), confirm attendance at ACHD clinic, and identify new or progressive complications (e.g., endocarditis, heart failure, stroke, thrombosis, systemic or pulmonary emboli, arrhythmia requiring drug or procedural intervention, renal or hepatic failure) [2]. Discrepant adjudication will be resolved by a cardiologist team member.Frequency and content of verbal and written (email/text messaging/telephone) dialogue between intervention nurse and participant. The intervention RN will complete detailed post-intervention field notes after each session. Telephone communication (phone calls, text messages) and emails will be encouraged from participants at any time; all will be recorded verbatim and analyzed (see Quantitative data analysis below).

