### Proposed sample size

The sample size is based on testing group differences in the primary outcome, excess time to ACHD care, with a two-sided log-rank test. A sample size of 60 patients per group (120 total) will allow detection of a difference between 90 and 70 %, the proportions that have attended their first ACHD clinic appointment by the end of the observation period in the intervention and usual care groups, respectively, with 80 + % power (Type I Error Probability [α] = 0.05), accounting for the “design effect” due to the cluster randomization of the trial. The proportion of 70 % in the usual care group is conservative, as published SickKids data suggests it may be as low as 50 % [8]. If the proportion of usual care participants attending the ACHD clinic is <70 %, the study power will be even higher. The difference between 90 and 70 % is the minimum clinically important difference, as a proportion <90 % attending ACHD care is unacceptably low [15]. Given that the most common reason for a lapse in care prior to first ACHD visit is a belief that cardiac follow-up is not required [9], a misconception that the intervention will address, we believe that a 90 % ACHD clinic attendance in the intervention group is achievable.

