### Quantitative data analysis

Intention-to-treat analysis will be used and all statistical tests will be two-sided. Baseline characteristics of the control (usual care) and intervention groups will be summarized using descriptive statistics (e.g., means, medians, standard deviations, frequencies, proportions). Kaplan-Meier plots will display excess time to first ACHD appointment by treatment group. Log-rank tests with a cluster-level bootstrap will test the difference in the excess time distribution between the intervention and control groups. The cluster sizes are likely to be 3–4. All statistical analyses will account for the cluster randomization. Participants who have not attended the ACHD clinic by the end of the study period (i.e., are censored) will still contribute to the primary outcome, as survival analysis is designed to accommodate censored data. We will assess differences in mean scores of each secondary outcome at baseline, 1, 6, 12, and 18 months, where applicable, by treatment group using general linear mixed models [24] that take both the cluster randomization and longitudinal nature of the data into account. Additional analyses will be stratified by a) study site (Edmonton versus Toronto) and b) attended first ACHD appointment (yes/no).

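### The secondary score analysis names arm differences in mean score at each visit, baseline included, while the outcomes are defined as change; a baseline-adjusted contrast at follow-up visits would be clearer and more precise

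*Protocol article*

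**What the plan says.** In the Protocol article, Quantitative data analysis sets the comparison for the secondary scores: "We will assess differences in mean scores of each secondary outcome at baseline, 1, 6, 12, and 18 months, where applicable, by treatment group". The sentence goes on to name the method: "using general linear mixed models [24] that take both the cluster randomization and longitudinal nature of the data into account". It lists no covariates and names neither a change contrast nor a group-by-time contrast.

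Two other sections describe the target differently. Background gives the aims as "1) change in adolescent knowledge of their CHD, 2) change in self-management and self-advocacy skills using validated instruments". Secondary outcomes defines the first score as "Change in MyHeart scores between baseline, 1, 6, 12 and 18 months" and the second as "Change in Transition Readiness Assessment Questionnaire (TRAQ) score between baseline, 1, 6, 12, and 18 months"; the Williams' Scale is defined in the same way.

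On timing, Secondary outcomes states: "All baseline questionnaires will be completed in the pediatric clinic, and prior to Session One for those in the intervention arm". The baseline score is therefore planned for every participant and is measured before treatment in the intervention arm. Usual care adds that randomization is stratified by site, and Group allocation that the randomized unit is the clinic week.

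**The concern.** The stated comparison and the stated outcomes are different quantities. A difference between arms in mean score at month 6 is a difference in level; the outcome definition calls for a difference in change. Nothing in the analysis sentence connects the two.

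Listing baseline among the compared visits gives it the wrong role. A between-arm difference measured before Session One cannot be an effect of the intervention, and the descriptive baseline summary is already covered by a separate sentence in the same section.

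At stake are the width of the intervals for three secondary scores and how far a chance baseline difference carries into the follow-up comparisons, in a trial with 60 participants per arm.

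**Working it through.** **The plan's own figure.** The only power statement concerns the primary outcome: "A sample size of 60 patients per group (120 total) will allow detection of a difference between 90 and 70" per cent. Under proportional hazards the hazard ratio is ln(0.10)/ln(0.30) = 1.912, with 60 × 0.9 + 60 × 0.7 = 96 events. The Schoenfeld formula gives 88.8% power without clustering and 81.1% at a design effect of 1.25 (cluster size 3.5, assumed ICC 0.10). The stated power of at least 80% is reproducible on that basis. No power or precision is stated for the secondary scores, so there is no figure to reproduce for this point.

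**Inputs.** 60 per arm (Proposed sample size). TRAQ SDs of 1.02 for self-management and 0.77 for self-advocacy (Secondary outcomes, from a cited field test in 194 youth with special healthcare needs). Two-sided alpha 0.05 is the trial's; 80% power for the scores is chosen here for illustration. The baseline-to-follow-up correlation ρ is an assumption, shown from 0.3 to 0.8. Design effect and dropout are left out.

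**Formulas.** The variance of the arm difference at one follow-up visit, relative to that of the visit-specific difference, is:

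- visit-specific difference: 1
- difference in unadjusted change: 2(1 − ρ)
- baseline-adjusted difference (covariate, or baseline means constrained equal): 1 − ρ²

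A generalized least squares check (five visits, complete data, compound symmetry, 60 per arm) gave the same ratios. With baseline as an unconstrained response, the visit-specific difference has a standard error of 0.183 SD at every ρ, which equals √(2/60). With complete data, the mixed model alone therefore adds no precision to that contrast.

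**Detectable difference, TRAQ self-management.** SE = 1.02 × √(2/60) = 0.186. Multiplied by 1.96 + 0.84 = 2.80, this gives 0.52 points. The adjusted figure is 0.52 × √(1 − ρ²). The last row of the table is power for a true difference of 0.5 SD, against 78% for the visit-specific difference.

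| Assumed ρ | 0.3 | 0.5 | 0.7 | 0.8 |
|---|---|---|---|---|
| Relative variance, unadjusted change | 1.40 | 1.00 | 0.60 | 0.40 |
| Relative variance, baseline-adjusted | 0.91 | 0.75 | 0.51 | 0.36 |
| Variance reduction from adjustment (ρ²) | 9% | 25% | 49% | 64% |
| Detectable, self-management (0.52 unadjusted) | 0.50 | 0.45 | 0.37 | 0.31 |
| Detectable, self-advocacy (0.39 unadjusted) | 0.38 | 0.34 | 0.28 | 0.24 |
| Power for 0.5 SD, baseline-adjusted | 82% | 89% | 97% | 99.5% |

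**Chance imbalance.** With an SE of 0.183 SD, a baseline difference larger than 0.2 SD in either direction (0.2/0.183 = 1.09 standard errors) arises in about 27% of trials of this size, before any design effect. A level contrast carries it forward in proportion to ρ: 0.2 SD becomes 0.10 SD at ρ = 0.5 and 0.14 SD at ρ = 0.7.

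**Change versus adjustment.** Unadjusted change would match the outcome wording, but it is less precise than the visit-specific difference when ρ is below 0.5. Baseline adjustment is more precise than either at every ρ in the table.

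**The case against.** The strongest reply is that the sentence is a summary in a journal article. It names a longitudinal mixed model over the same five visits used in the outcome definitions. Group-by-time terms in that model would estimate arm differences in change, and constraining the baseline means to be equal, which requires baseline among the responses, would give the full precision of adjustment. Covariates and contrasts are commonly left to the full protocol or analysis plan, which is not shown.

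Much of this stands. A reader might infer that raw visit means will be compared, or that the trial has decided against baseline adjustment. The document supports neither: the means are model-based, and the text is silent on adjustment rather than opposed to it. A reader might also infer bias. In a randomized comparison, leaving out the baseline score costs precision but does not in itself bias the estimate. Recruitment that differs by week is conceivable, because participants, parents and study nurses know the allocation, but nothing in the document shows it, and clinic support staff and cardiologists are blinded.

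It is also fair that the secondary aims are introduced as descriptive, that no power is claimed for the scores, and that the gain is small if ρ is low.

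The reply does not remove what is written. The named quantity is a difference in level, baseline is one of the visits at which arms are compared, and the outcomes are defined as change. A model that could supply a better contrast is not the same as a plan that names it.

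**Conclusion.** The point holds as a minor one. Quantitative data analysis should name a contrast that agrees with Background and Secondary outcomes, use the baseline score, and stop listing baseline as a compared visit. If the visit-specific differences were reported as written, the avoidable variance would be 9% to 64% of the total for ρ from 0.3 to 0.8.

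That size rests on an assumed correlation applied equally to visits from 1 to 18 months, on complete data, and on no design effect. The TRAQ figures in points also rest on SDs from another population. The point covers only MyHeart, TRAQ and the Williams' Scale. It does not extend to re-intervention, the cardiologist questionnaire or the nurse-participant dialogue, and it should not be read as a doubt about the primary outcome or its sample size.

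**What to change.** Keep the longitudinal mixed model and state three things in it: the baseline score as a covariate, site as a fixed effect (randomization is stratified by site), and week as a random effect. Constraining baseline means to be equal across arms is an alternative with the same precision under complete data, but the covariate is safer if recruitment may differ between intervention and usual care weeks, because the constraint would then be doubtful.

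Report baseline-adjusted arm differences at 1, 6, 12 and 18 months only. Leave baseline to the descriptive summary. Then align the wording of the aims in Background, the definitions in Secondary outcomes and the sentence in Quantitative data analysis, so that all three name the same quantity.

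The cost is a sentence or two of text. The baseline scores are already planned for all participants, so no extra data or visits are needed. If the full analysis plan already specifies this, only the article's wording needs to be brought into line.

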### Outcome measures

Outcome measures correspond to aims as described above. The *primary outcome* will be the excess time between pediatric and ACHD care, defined as the time interval (in months) between the final pediatric visit and the first ACHD visit, minus the recommended time interval between these visits. The “recommended time” interval will be the interval suggested by the cardiologist at the final pediatric visit. For example, if the time between the final pediatric visit and first ACHD visit was 20 months but the pediatric cardiologist recommended this be 12 months, the excess time would be 8 months. If the first ACHD visit takes place before the recommended time, the excess time will be zero. For the rare study participant not having a documented “recommended time”, recommendations for frequency of care will be taken from published guidelines [22, 23]. Excess time to ACHD care is an objective and clinically meaningful outcome, as lapses between pediatric and ACHD care result in increased cardiac morbidity and need for re-intervention [9]. First ACHD appointments that occur 2 or more months later than had been recommended by the referring pediatric cardiologist will result in a review of medical records to identify potential participant or system factors, including a) ACHD waiting list too long to accommodate participant when recommended, b) ACHD team unaware of initial referral, or c) participant did not agree to an earlier appointment.

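### Additional analyses are to be stratified by whether the first ACHD appointment was attended, a post-randomisation variable that the intervention is meant to change, so arm comparisons within those strata are not randomised comparisons

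*Protocol article*

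**What the plan says.** Quantitative data analysis opens with "Intention-to-treat analysis will be used and all statistical tests will be two-sided". It then gives the primary test, "Log-rank tests with a cluster-level bootstrap will test the difference in the excess time distribution between the intervention and control groups", and the secondary-score comparison, which is made "by treatment group using general linear mixed models". It closes with "Additional analyses will be stratified by a) study site (Edmonton versus Toronto) and b) attended first ACHD appointment (yes/no". That last sentence names no outcome, does not say whether arms will be compared within the strata, and lists attendance beside site without distinguishing the two.

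Other sections fix what attendance is:

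- Outcome measures defines the primary outcome as "the time interval (in months) between the final pediatric visit and the first ACHD visit, minus the recommended time interval between these visits". The first ACHD visit is therefore the event.
- Quantitative data analysis treats those without the event as censored: "Participants who have not attended the ACHD clinic by the end of the study period (i.e., are censored").
- Proposed sample size expects 90% in the intervention group and 70% in usual care, described as "the proportions that have attended their first ACHD clinic appointment by the end of the observation period".
- Measurement of outcomes at follow-up has the first ACHD visit documented at chart review at 12 and 24 months. The questionnaires run from baseline to 18 months.

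**The concern.** A stratification factor for a treatment comparison should be fixed before randomisation. Site meets that condition. Attendance does not: it happens later, and moving it is the purpose of the trial.

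If the intervention raises attendance, the two arms' attenders are different kinds of people. The intervention arm's attenders include some who would have stayed away under usual care, and its non-attenders are a smaller, more selected remainder. Comparing knowledge or readiness scores between arms inside either group then mixes any treatment effect with this selection. The article makes a link between scores and attendance plausible: it attributes lapses largely to a mistaken belief that follow-up is unnecessary, and the TRAQ covers arranging follow-up visits.

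Timing adds to the difficulty. A score at 1 or 6 months could be grouped by an event recorded only at the 24-month review, so the analysis would condition on the future. It also sits awkwardly beside the intention-to-treat commitment in the same paragraph.

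At stake is a supplementary result that may disagree with the main analyses and be read as a treatment effect.

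**Working it through.** **Inputs.** 60 per group; attendance 90% and 70%; two-sided alpha 0.05; stated power of at least 80% for a log-rank test; clusters of 3 to 4 (Proposed sample size and Quantitative data analysis). The article gives no intracluster correlation (ICC), no correlation r between scores and attendance, and no attendance mechanism. These are assumed below.

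**1. The plan's own figure.** Hazard ratio = ln(0.10)/ln(0.30) = 1.912. Expected events = 60 × (0.90 + 0.70) = 96. By the Schoenfeld formula, power = Φ(√(96/4) × ln 1.912 − 1.96) = 88.8% with no design effect. It stays at or above 80% up to a design effect of about 1.28. With design effect 1 + (m − 1) × ICC, that is an ICC of about 0.14 at m = 3 or 0.09 at m = 4. The stated power is reproduced for small to moderate ICC and does not depend on the stratification.

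**2. Expected strata, if attendance means attended by study end.**

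| | Intervention | Usual care |
|---|---|---|
| Attended | 60 × 0.90 = 54 | 60 × 0.70 = 42 |
| Not attended | 60 × 0.10 = 6 | 60 × 0.30 = 18 |

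**3. Selection when the score is unaffected.** Assume a standard normal readiness trait, attendance above a threshold, and an intervention that only lowers the threshold, so that the top 90% attend and not the top 70%. The score has correlation r with readiness and no treatment effect.

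- Mean readiness of attenders: φ(1.282)/0.9 = 0.195 and φ(0.524)/0.7 = 0.497. Difference -0.302.
- Mean readiness of non-attenders: -φ(1.282)/0.1 = -1.755 and -φ(0.524)/0.3 = -1.159. Difference -0.596.

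The spurious difference in score, intervention minus usual care, is r times these:

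| r (assumed) | Attenders | Non-attenders |
|---|---|---|
| 0.2 | -0.06 SD | -0.12 SD |
| 0.3 | -0.09 SD | -0.18 SD |
| 0.5 | -0.15 SD | -0.30 SD |

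**4. Selection when the intervention raises readiness.** Keep the threshold fixed and shift readiness by 1.282 − 0.524 = 0.758 SD, which gives the same 90% and 70%. The arm difference in readiness is then:

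- attenders: 0.758 + 0.195 − 0.497 = +0.46 SD;
- non-attenders: 0.758 − 1.755 + 1.159 = +0.16 SD.

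Both favour the intervention, but both fall short of the true 0.758 SD.

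**5. If the stratification were also applied to excess time.** With the step 2 definition, the not-attended stratum has 24 participants and no events, so a log-rank test there is undefined. The attended stratum has 96 participants, all with events. In 4,000 simulated trials with exponential times and no clustering, power among attenders alone was 26%, against 88% in everyone. If the intervention changed only whether participants attend and not when, rejection among attenders was 5%, which is the nominal level, against 71% in everyone.

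**The case against.** The sentence is brief and part of a condensed article. It promises no between-arm test within attendance strata and may mean only that scores will be described separately for attenders and non-attenders, which would be acceptable. That stands as a reason to clarify. It does not remove the point: the sentence follows two by-arm analyses, pairs attendance with site, and carries no descriptive label. This is a stated analysis, not a detail left to another document.

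Three stronger readings are tempting and are not supported.

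- A reader might infer that the primary endpoint analysis is degenerate. The sentence names no outcome and comes directly after the secondary-score models. Nothing says the log-rank test will be rerun within these strata, so step 5 is conditional. Attendance could also mean keeping the first booked appointment, since Usual care describes telephoning non-attenders to reschedule. Some in the no group would then have events later and the 6 against 18 split would not follow. The factor would still be post-randomisation.
- A reader might infer that the intervention must look worse in both strata the better it works. That needs the model of step 3. Step 4 uses the same truncated-normal figures and gives positive differences. System causes of late attendance, such as waiting lists, would also weaken r.
- A reader might infer that the trial's randomised comparison is lost. It is not: the primary test and the main mixed models compare all participants by assigned group.

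**Conclusion.** The point holds for the supplementary analysis only. Stratifying treatment comparisons by attendance conditions on a post-randomisation variable that is essentially the primary event and is expected to differ by 20 percentage points between arms. The loss of comparability follows from the article's own definitions and rates, provided scores and attendance share causes.

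Neither the size nor the direction of the bias can be fixed from the article. Under a zero-effect threshold model it is -0.30r and -0.60r SD; under a readiness-shift model a true 0.758 SD appears as 0.46 and 0.16 SD. The r values and both mechanisms are illustrative assumptions. The impossibility of a test among non-attenders applies only if excess time is included and the no category means not attended by study end. It is worth correcting before analysis.

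**What to change.** Replace the closing sentence of Quantitative data analysis so that stratified treatment comparisons use site only. If the relation between scores and attendance is of interest, choose one of two routes and say which:

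- describe scores of attenders and non-attenders, pooled or within arm, with no between-arm test, and state the definition and cut-off date of attendance; or
- treat attendance as an outcome or a mediator in a prespecified analysis labelled exploratory, with its assumptions stated and clustering by week respected.

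The cost is one sentence. No new data, visits or participants are needed, and the primary test, main mixed models and sample size stay as they are.
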